### Sample size

The sample size is calculated with 80% power and 5% test error (95% confidence interval), based on a similar study by Gil
*et al.*
^39^:

$$\text{n}=\frac{\left(z_{1-\alpha /2}+z_{1-\beta }\right)2\left({s_{1}}^{2}+{s_{2}}^{2}\right)}{{\left(\mu_{1}-\mu_{2}\right)}^{2}}$$

According to the abovementioned formula and a 20% dropout rate, the sample size is estimated to be 22 in this study (11 participants per group).

### Data analysis

First, the Chi-square test will be used to examine the normal distribution of each variable. If data distribution is normal, parametric tests, including paired t-test, independent t-test, and ANCOVA test, will be performed. Otherwise, non-parametric Mann-Whitney and Wilcoxon tests will be carried out. Fisher’s exact test will be applied for the homogeneity of the groups. Statistical analysis will be conducted using SPSS version 22.0 (IBM Corporation, New York, USA), and the significance level is considered to be 0.05.

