^39^. Therefore, after the study population is selected, the designed auditory training program will run only for the intervention group over three months. The program will be provided as a DVD to the intervention group for use at home (at home PC-based training program). The auditory training program will be carried out in three easy, medium, and hard stages, with each stage consisting of 12 levels (sessions). Each stage will continue for one month and will be performed by the user for three sessions per week (30–40 minutes per session).

In the designed program, the difficulty of training increases from level 1 to level 36, and the user’s task becomes more difficult requiring more precision. The program is based on the repetition of exercises. In each session, the user is required to earn more than 80% of the scores to pass to the next level. All of the exercises will be performed in several stages over a three-month auditory training period. The exercises start from easy levels in the early days to difficult levels in the final weeks. The program will be implemented at MCL for users with hearing aids in the free field.

To fully familiarize the user with the auditory training program, the first three sessions of the program will be conducted in the audiology clinic in the presence of the researcher to ensure that the user has learned how to use the program correctly and that it is executed properly. Subsequent home sessions will be conducted according to the program protocol and the training of each part of the program. However, in order to retain control and ensure that the program is performed correctly, in all rehabilitation sessions at home, users will be monitored by the researcher via a phone or video call. If a participant is unable to run the program after these tutorials and tips, the training will be discontinued and the person will be removed from the study.
****

3. Assessments after the implementation of the auditory training program

In this stage, central tests, including GIN, DPT, QuickSIN, and speech ABR test, will be repeated for both the control and intervention groups immediately after auditory training, and the outcomes will be compared with the pre-training results. The tests will be repeated after one month to determine the reliability of intervention results to improve the users’ temporal processing.

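### A chi-square normality test that is unreliable with 22 participants decides, outcome by outcome, whether the baseline-adjusted group comparison (ANCOVA) is used

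*Protocol article*

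**What the plan says.** The Data analysis section of the protocol article sets a two-step rule. The first step is a normality check: "First, the Chi-square test will be used to examine the normal distribution of each variable". The second step depends on the result. "If data distribution is normal, parametric tests, including paired t-test, independent t-test, and ANCOVA test, will be performed". If the check fails: "Otherwise, non-parametric Mann-Whitney and Wilcoxon tests will be carried out". The threshold is stated as "the significance level is considered to be 0.05".

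The section does not say whether normality is tested per group or pooled, how many cells are used, whether Mann-Whitney is applied to post-training scores or to changes, or which of the two parametric between-group tests decides.

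Two other sections bear on this. Sample size gives "a 20% dropout rate, the sample size is estimated to be 22 in this study (11 participants per group". Study procedures has every outcome test done in both groups before training, immediately after it and one month later. It says of the repeat tests that "the outcomes will be compared with the pre-training results". A baseline value of each outcome is therefore available for adjustment.

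**The concern.** Choosing the analysis by a preliminary normality test is only as good as that test. A chi-square goodness-of-fit test must bin the data and spends two degrees of freedom on the fitted mean and SD, so it is a weak choice in very small samples. It is also aimed at the wrong target. The t-test and ANCOVA rest on the distribution within groups or of the residuals, whereas pooled post-training scores mix two groups that the trial expects to differ.

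The outcome of the gate has consequences. ANCOVA stands only in the normal branch, so an outcome that fails loses covariate adjustment in its group comparison. Because the gate is applied to each variable separately, the trial's outcomes may be analysed by different methods for reasons close to chance. Within the parametric branch, two between-group tests are listed with neither named as deciding, which leaves room for a choice that raises the false-positive rate.

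**Working it through.** **Inputs.** From the protocol article: 11 per group, 20% dropout, 80% power, two-sided 5% level. Completers: 11 × 0.8 = 8.8, about 9 per group; 22 × 0.8 = 17.6, so 17-18 in all. Assumed, because the article gives no means, SDs or correlations: the effect size, the pre-post correlation r and the non-normal shape.

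**1. The plan's own figure.** The sample size of 22 cannot be reproduced without means and SDs. Only the implied standardised effect can be back-solved, taking the sum of the two z-values in the formula as squared: d = (1.960 + 0.842) × √(2/n). This gives 1.34 for n = 8.8, 1.32 for n = 9 and 1.19 for n = 11. I use 1.34 as the assumed effect, and 1.32 and 1.0 for the range.

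**2. Degrees of freedom of the gate.** df = cells − 1 − 2. With at least 5 expected per cell, the number of cells is n/5 rounded down.

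| Sample tested | n | Cells | df |
|---|---|---|---|
| One group, completers | 9 | 1 | −2 |
| One group, all | 11 | 2 | −1 |
| Pooled completers | 17-18 | 3 | 0 |
| Pooled, all | 22 | 4 | 1 |

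**3. Behaviour of the gate if the expected-count rule is ignored.** Simulation with 4 equal-probability cells, fitted mean and SD, 1 df, nominal 5%:

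| n | Rejects normal data | Detects exponential data |
|---|---|---|
| 11 | 10% | 26% |
| 18 | 9% | 31% |
| 22 | 8% | 31% |

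Shapiro-Wilk detects exponential data 49% of the time at n = 11 and 87% at n = 22. With 5 cells the chi-square test is better calibrated (5% at n = 11, 8% at n = 22), but it still detects exponential data only 26% and 43% of the time.

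**4. Power for the group comparison, by branch.** Simulation, 9 per arm, normal data:

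| Assumed d | r | ANCOVA | Mann-Whitney, post | Mann-Whitney, change |
|---|---|---|---|---|
| 1.34 | 0.5 | 83% | 70% | 69% |
| 1.34 | 0.7 | 95% | 69% | 89% |
| 1.32 | 0.3 | 74% | 68% | 52% |
| 1.32 | 0.8 | 99% | 69% | 97% |
| 1.0 | 0.5 | 61% | 46% | 45% |
| 1.0 | 0.7 | 79% | 46% | 68% |

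At d = 1.34 the loss is 83 − 70 = 13 to 95 − 69 = 26 points on post scores, and 95 − 89 = 6 to 83 − 69 = 14 points on changes.

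**5. Is the switch needed for validity?** In simulation, ANCOVA keeps a type I error of about 4-5% under both normal and exponential errors. In those settings the switch buys no protection.

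**6. Average cost over the gate.** The loss in step 4 arises only when an outcome fails. For normal data at n = 18 the gate fails 9% of the time. The average loss is then roughly 0.09 × 6 = 0.5 to 0.09 × 26 = 2.3 points, if failing the gate is unrelated to the size of the loss.

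**7. Two listed tests, none deciding.** Taking the smaller p-value of the independent t-test on post scores and ANCOVA gives about 7-8% type I error at a nominal 5%.

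**8. More covariates.** If age and gender are added to the ANCOVA and are not prognostic, power with 18 completers falls from 83% / 95% to about 77% / 90% (r = 0.5 / 0.7), a loss of 6 and 5 points.

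**The case against.** The strongest defence is that four tempting readings go beyond the text.

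- **The test cannot be computed.** A reader might infer this from the degrees of freedom. It needs a per-group test and the expected-count rule, and the article states neither. It speaks of variables, not groups. Pooling all 22 leaves 1 df, and a cruder version with small cells can be run. What stands is that the versions that can be run are weak, and with 4 cells they also over-reject.
- **The fallback discards the baseline.** The article does not say so. Wilcoxon, as counterpart of the paired t-test, uses the baseline within a group, and Mann-Whitney can be run on changes. With normal data and r = 0.7 the gap to ANCOVA is then 6 points rather than 26, and with exponential errors at r = 0.7 simulation shows none. What stands is that covariate adjustment is lost and the score is left open.
- **The whole trial loses this power.** The loss applies only to outcomes that fail, and a normal outcome usually passes into the branch that contains ANCOVA. Averaged over the gate, the cost for normal data is about 0.5 to 2.3 points.
- **The choice of test doubles the false-positive rate.** A figure near 10% arises only if a change-score t-test is added, which the article does not list. For the two listed tests it is 7-8%, and only if the better result is chosen. The independent t-test may be meant for baseline or unadjusted comparisons.

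It is also fair to say that cell counts, the score used and the order of tests are details that an article may leave to an analysis plan. That does not answer the point. The gate and the switch are stated rules, and an analysis plan that followed them would inherit the problem.

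**Conclusion.** The point holds in limited form. The article makes an unreliable normality test decide whether the only covariate-adjusted between-group method is used. For an outcome that fails, power drops by about 6 to 26 points at the assumed 1.34 SD effect and r of 0.5 to 0.7. Where in that range it falls depends mainly on r and on whether Mann-Whitney is run on post scores or changes. The lack of a deciding test in the parametric branch puts the type I error at up to about 7-8%.

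The df result is arithmetic under the expected-count rule. The power figures rest on an assumed effect, assumed correlations and 9 completers per arm, and the direction in favour of ANCOVA is the same across the normal-data scenarios tabulated. The documents do not support saying that the test cannot exist, that the baseline is always thrown away, or that the whole trial loses this much power. This should be fixed, but it does not by itself invalidate the trial.

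**What to change.** Delete the chi-square check and the switch between test families. In their place, state that for every outcome, at each of the two post-training visits, the between-group analysis is ANCOVA of the post-training score on group with the same outcome's baseline value as covariate, whatever the distribution. Judge fit by residual plots. Name one robustness check in advance: a permutation p-value from the same ANCOVA, or ANCOVA on ranks. Paired tests may remain as within-group description, and an independent t-test should not stand as an alternative group comparison.

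Age and gender need not be required as covariates. With 18-22 people they cost about 5-6 points of power if they are not prognostic, and the article gives no information on whether they are.

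The cost is a change of wording and one extra sensitivity run. ANCOVA is already in the plan. The Study status section says allocation has not yet been done, so the change can be made before any post-training result is seen.

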### Study status and dissemination of findings

This trial will start in April 2020 and will be completed in September 2020. To date, enrolment of patients has been performed, and allocation will be done shortly. The trial outcomes will be published in the relevant scientific journals and the results will be communicated to the public, participants and audiologists through a formal report. The results of this study will be communicated to the external funding body through a formal report and there is no limit on the publication of the trial results.

## Discussion

Age-related hearing loss not only influences the physical and emotional activities of the elderly, but also affects their social activities and reduces their quality of life due to various factors, such as depression, social isolation, and reduced self-confidence. One of the important problems in maintaining and promoting the health and quality of life of the elderly is to maintain their independence in daily life activities and to provide suitable conditions for them to continue an active and independent life
^40,
41^. Therefore, by implementing a proper auditory training program, the elderly can comprehend speech in noisy environments; this, in turn, prevents their isolation and reduces the social and financial burdens of their disabilities.

The “plasticity” phenomenon, which has been scientifically approved, suggests the efficacy of auditory training in improving the speech comprehension skills of the elderly. So far, various auditory training methods have been introduced and applied to different studies
^42^. In Iran, we need to design and develop such methods based on the elderly’s needs. Multiple studies have been performed on auditory training for children after receiving hearing aids. However, in Iran, auditory training for elderly users of hearing aids has not been studied, and this is the first research conducted in our country. For this purpose, an elderly auditory training program was designed and implemented with an emphasis on the temporal aspects of speech. Also, regarding the need for special tools and facilities to establish this auditory training program, the proposed program can be used in audiology clinics and academic centers to improve the speech comprehension of elderly users of hearing aids, especially in the presence of background noise.

## Data availability

### Underlying data

No underlying data are associated with this article.

### Extended data

Open Science Framework: The effects of a temporal processing-based auditory training program on the auditory skills of elderly users of hearing aids: a study protocol for a randomized clinical trial.
https://doi.org/10.17605/OSF.IO/SB934
^30^

This study contains the following extended data:
Consent form for participants of the study.docxTable 1 (Details and steps of the rehabilitation program).xlsxTable 2 (Schedule of temporal processing-based program).docxTable 3 (The data collection sheet of the study).docxTable 4 (Participant timeline).docx

### Reporting guidelines

Open Science Framework: SPIRIT checklist for 'The effects of a temporal processing-based auditory training program on the auditory skills of elderly users of hearing aids: a study protocol for a randomized clinical trial':
https://doi.org/10.17605/OSF.IO/QPJDK
^30^.

Data are available under the terms of the
Creative Commons Attribution 4.0 International license (CC-BY 4.0).

## Software availability

Source code available from:
https://github.com/[name]/source-code-of-auditory-training/tree/V2.0.0

Archived source code at time of publication:
https://doi.org/10.5281/zenodo.3816735
^31^

License:
MIT
